### Additional consent provisions for collection and use of participant data and biological specimens {26b}

All the biological specimens used in the study were collected in the routine follow-up of the patients.

## Interventions

### Explanation for the choice of comparators {6b}

The two kidneys coming from one donor will be randomly allocated: one to the standard-of-care arm (organ preserved in preservation solution routinely used according to the local practice) and the other to the active treatment arm (HEMO_2_life® on top of routinely used preservation solution).

### Intervention description {11a}

HEMO_2_life® will be used for ex vivo graft preservation by diluting it to 1 g/l in preservation solution. For static cold storage, the kidney will be perfused on the back table with 100–150 ml of the preservation solution plus HEMO_2_life® to allow the release of the oxygen carrier inside of the kidney. Then, the kidney will be transferred to the storage container containing the rest of the mix (850–900 ml). For machine-perfused grafts, 1 g of HEMO_2_life® will be added to 1 l machine perfusion solution, and kidney placement on the machine will be performed according to the usual company protocol. In both situations, the kidney will be rinsed just before transplantation with the plain preservation solution (with no HEMO_2_life®) to flush out any residual molecules of HEMO_2_life® and until the liquid becomes clear.

### Criteria for discontinuing or modifying allocated interventions {11b}

Not applicable, treatment is administrated ex vivo.

### Strategies to improve adherence to interventions {11c}

Not applicable, treatment is administrated ex vivo.

### Relevant concomitant care permitted or prohibited during the trial {11d}

The study does not forbid any treatment. No specific immunosuppressive regimen is imposed by the protocol, and the immunosuppressive strategy is left to the discretion of the renal transplant center. All concomitant medications taken during the study will be documented in the patient records and in the eCRF.

### Provisions for post-trial care {30}

There is no anticipated harm and compensation for trial participation.

### Outcomes {12}

Primary outcome: The primary outcome is the occurrence of DGF, defined as the need for renal replacement therapy during the first week after transplantation.Secondary outcomes: Efficacy and safety secondary outcomes will be collected.

*Efficacy*: for comparison of the two groups and specific subgroups of donors (static preservation, machine preservation, type of preservation solution, ECD, DCD and standard donors) and recipients (diabetes, obese, etc.):rate of PNF.graft and patient survival at one year.rate of biopsy-proven acute rejection at one year.DGF, assessed with alternative definitions: more than one dialysis session, need for dialysis except for hyperkaliemia or overhydration reason, time to reach a creatinine value of 250 µmol/l, and number of dialysis sessions.renal function (creatinine value and estimated glomerular filtration rate (eGFR)) at Days 7, 14, and 30 and months 3 and 12; areas under the concentration curves (AUCs) of creatinine and eGFR from D0 to D30.protocol biopsy analysis (preimplantation and at month 3) in a subgroup of 100 patients per group: A) comparison of the chronic scores of tubule-interstitial damage according to the Banff classification [29]: tubular atrophy (ct score ranging from 0 to 3) and chronic interstitial fibrosis (ci score ranging from 0 to 3); and of vascular damage: fibrous intimal thickening (cv score ranging from 0 to 3) and arteriolar hyalinosis (ah score ranging from 0 to 3). B) Analysis of interstitial fibrosis using automated quantitative image analysis (Institut Pasteur-France) and comparison of the progression of interstitial fibrosis in a subgroup of 100 patients per group.quality of life: at 1, 3 and 12 months, using the generic self-administered questionnaire EQ-5D and a specific questionnaire for renal transplant recipients in the French language: the ReTransQol (RTQ) [30].

#### Safety

The safety profile of the medical device HEMO_2_life® will be assessed. In particular, all incidents and events of interest occurring during the use of HEMO_2_life® will be collected, including packaging issues, difficulty of mixing HEMO_2_life® into the preservation liquid, perfusion issues, machine perfusion issues, macroscopic aspects of the preservation solution containing HEMO_2_life®, contamination of the conservation solution, macroscopic aspects of the graft before transplantation, and surgical difficulties.

Grafts and patient safety will be investigated by collecting all AEs during the first month and all serious AEs up to one year. These events will be analyzed by the sponsor safety and biovigilance department.

### Participant timeline {13}

The kidney recipient will be followed from transplantation to 1 year after transplantation. The clinical and laboratory data of patients will be collected at D0, D1, D3, D7, D14, M1, M2, M3 and M12 (see Table 1).

**Table 1 Tab1:**
[figure not shown]
The clinical and laboratory data of patients will be collected at D0, D1, D3, D7, D14, M1, M2, M3 and M12. DGF: Delayed graft function

### Sample size {14}

This sample size is based on the confirmatory testing strategy described below, according to Alosh and Huque’s methodology [31]. This methodology allows us to make inferences on the overall population and/or on a prespecified subgroup (graft preserved in cold storage) while controlling for the familywise error rate (FWER).

This proposed methodology requires first testing global efficacy at a reduced alpha level, chosen here to be 0.03. In the 3 cumulating years 2015 to 2018 the mean rate of DGF in France was 28% according to the data of Agence de la Biomédecine (https://rams-archives2019.agence-biomedecine.fr/sites/default/files/2021-01/LE%20RAPPORT%20M%C3%89DICAL%20ET%20SCIENTIFIQUE%20DU%20PR%C3%89L%C3%88VEMENT%20ET%20DE%20LA%20GREFFE%20EN%20FRANCE2.zip). The sample size calculation rests on an expected DGF rate of 28% in the control arm and a 15% rate in the HEMO_2_life® arm. To guarantee 80% power to detect such a difference at this first step, the minimum sample size per group is 180 evaluable grafts. Expecting 20% of nonevaluable inclusions, a total of 450 patients (225 pairs) are needed.

### Recruitment {15}

We anticipate 10 to 15% of preemptive grafts in the protocol. These kidneys will not be analyzed in the paired analysis for the primary endpoint because they are less likely to require hemodialysis. Therefore, enrollment will be continued until the required sample size in terms of evaluable paired kidneys (180 pairs) is achieved. In total, we expect to include approximately 260 donors in the study.

Nonevaluable inclusions include discordant pairs according to the type of conservation (cold storage/perfusion machine) as well as nontransplanted grafts.

## Assignment of interventions: allocation

### Sequence generation {16a}

Randomized allocation will be achieved through "Ennov Clinical", a secure server with access to the e-CRF, by the retrieving investigational team. The randomization will be stratified according to the donor type (standard donor/ECD/DCD) and the destiny of the kidney (local kidney/contralateral kidney).

### Concealment mechanism {16b}

Use of a validated password website using a secure server will ensure concealment.

### Implementation {16c}

The surgeon in charge of the organ procurement is responsible for the randomization and the administration of the medical device.

## Assignment of interventions: Blinding

### Who will be blinded {17a}

The use of HEMO_2_life® results in a red coloration of the preservation solution, so a double-blind study is not possible. This explains why we designed a single-blind study: the graft recipient will not be informed about the allocated arm.

### Procedure for unblinding if needed {17b}

The surgeon performing the renal transplantation is not blinded so unblinding will not be necessary.

## Data collection and management

### Plans for assessment and collection of outcomes {18a}

The kidney recipient will be followed from transplantation to 1 year after transplantation. All patients will be followed up. For safety reasons, we plan to follow each patient who has received a graft that has been perfused and stored in a preservation solution containing HEMO_2_life®, even if they refuse to participate in the study. In this case, only graft, donor and surgical information and AEs will be collected and recorded in a fully anonymized database, as the patients will not have given their informed consent for biological and clinical data collection.

The following data will be recorded: demographic data, medical history of the donor and the recipient, transplant surgical procedure and complications, vital signs, treatments given, and laboratory tests. Renal function will be assessed by measuring serum creatinine and eGFR using the MDRD formula [32] before surgery; at Days 0, 3, 7, 15, and 30 (but every extra creatinine measurement during the first month will be recorded as well); and at M3 and at M12 (Table 1). PNF, DGF, slow recovery of renal function, acute rejections and transplant dysfunctions will be recorded throughout the study. Biopsy analysis (at least before implantation and at month 3, performed routinely by the centers) will be analyzed by Banff classification [29] and by analyzing lesion evolution, especially that of interstitial fibrosis between the two biopsies (including quantification).

### Plans to promote participant retention and complete follow-up {18b}

For safety reasons, we plan to follow each patient who has received a graft that has been perfused and stored in a preservation solution containing HEMO_2_life®, even if they refuse to participate in the study. In this case, only graft, donor and surgical information and AEs will be collected and recorded in a fully anonymized database, as the patients will not have given their informed consent for biological and clinical data collection.

### Data management {19}

Data will be entered into the web-based electronic Case Report Form (eCRF) (……) under the supervision of the trial site investigators at each participating center. A Clinical Research Assistant (CRA) appointed by the sponsor will be in charge of the study data collection in writing, data recording, data saving and reporting in accordance with the sponsor Standardized Operating Procedures as well as the Good Clinical Practice guidelines and the in force legislation and laws. The investigator and the members of his/her team agree to be available during all the routine and planned Quality Control (QC) visits by the CRA. During these visits, the followings will be audited:Signed informed consentCompliance of the study’s protocol and its described proceduresQC of the collected data into the e-CRF: accuracy, missing data, consistency between these data and those of “source” (medical files, original of the laboratory results, etc.)

### Confidentiality {27}

The QC people as well as the investigators are subject to professional confidentiality (according to the French penal code articles 226–13 and 226–14). During the research or at its end, the collected data on the individuals undergoing the trial sent to the sponsor by the investigators (or any other specialized participant) will be anonymized.

### Plans for collection, laboratory evaluation and storage of biological specimens for genetic or molecular analysis in this trial/future use {33}

No specific biological samples were taken for this study. We verified before the start that all the data needed for the analysis were part of the routine blood samples performed in the transplant centers. Additionally, no biological specimens were stored for genetic or molecular analysis.

## Statistical methods

### Statistical methods for primary and secondary outcomes {20a}

Full Analysis Population:All complete and concordant (according to the type of conservation: cold storage or perfusion machine) randomized pairs fulfilling the inclusion criteria with no exclusion criterion.Preemptive grafts will be excludedRandomized pairs who do not receive HEMO_2_life® will be excluded, provided that HEMO_2_life® cancellation is not related to graft function.

Extended Full Analysis Population (exploratory):All randomized grafts fulfilling the inclusion criteria and no exclusion criterion will be included.Preemptive grafts will be excludedRandomized pairs who do not receive HEMO_2_life® will be excluded provided that HEMO_2_life® cancellation is not related to graft function.

#### Safety population

All subjects who receive any study treatment (including control) but excluding subjects who drop out prior to receiving any treatment will be included. Preemptive grafts will be included in the safety population.

Regarding renal function, only available data will be used in a first step that assumes that death and dialysis will be balanced in the two groups. A sensitivity analysis will then be performed using the last observation carried forward (LOCF) for deceased patients and a fixed value (eGFR = 5) for dialysis patients.

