### Objectives {7}

The present research focuses on the efficacy of HEMO_2_life® added to preservation solution in kidney transplantation.

The primary objective is:

To quantify the efficacy of HEMO_2_life® used as an additive to standard organ preservation solution to prevent DGF following renal transplantation.

The secondary objective is as follows:

To assess and compare graft and patient survival in the two groups (standard of care versus HEMO_2_life®)To assess the efficacy of HEMO_2_life® on renal parameters compared with the standard of care.To assess efficacy in specific populations with different donor types and preservation method (standard donors, ECD, DCD, SCS, machine perfusion, different perfusion solutions).To evaluate the impact of HEMO_2_life® on the degree and progression of interstitial fibrosis before implantation and in 3-month biopsies.To assess the safety profile of HEMO_2_life® for the graft and the graft recipient.

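### Graft safety is an objective, but kidneys not transplanted after randomisation are not compared between arms in any safety analysis the protocol states

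*Protocol article*

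**What the plan says.** All references are to the Protocol article.

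- **Objectives {7}** lists, among the secondary objectives, "To assess the safety profile of HEMO_2_life® for the graft and the graft recipient".
- **Intervention description {11a}**: the product "will be used for ex vivo graft preservation by diluting it to 1 g/l in preservation solution". The treated unit is the kidney.
- **Implementation {16c}**: "The surgeon in charge of the organ procurement is responsible for the randomization and the administration of the medical device". Randomisation and treatment thus come before implantation.
- **Recruitment {15}** expects some kidneys never to be implanted: "Nonevaluable inclusions include discordant pairs according to the type of conservation (cold storage/perfusion machine) as well as nontransplanted grafts".
- **Safety population**: "All subjects who receive any study treatment (including control) but excluding subjects who drop out prior to receiving any treatment will be included". The next sentence adds: "Preemptive grafts will be included in the safety population".
- **Safety** (under Outcomes {12}) lists incidents occurring during use of HEMO2life, such as perfusion problems, contamination of the solution and "macroscopic aspects of the graft before transplantation, and surgical difficulties". Discard is not on the list, and no matching collection is stated for control kidneys. Graft and patient safety are otherwise followed through adverse events to one month and serious adverse events to one year.
- **Safety analyses** gives one comparison between groups: adverse events by MedDRA Preferred Term, with a chi-square or Fisher test.

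**The concern.** The intervention acts on the organ between procurement and implantation. Harm in that interval, such as poor perfusion, contamination or an abnormal appearance, could end in the kidney not being used. Such a kidney has no recipient and so no adverse events.

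If graft safety is judged only through recipients' adverse events, the comparison is conditional on the kidney having been implanted. That decision need not be independent of arm. Who will be blinded {17a} says the product turns the solution red, and Procedure for unblinding {17b} says the transplanting surgeon is not blinded. The decision could be influenced in either direction.

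At stake is whether the trial can answer the graft half of its own safety objective. The design is well suited to do so, because every randomised kidney has its partner from the same donor in the other arm.

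**Working it through.** **1. The plan's own figures.** The inputs, from Sample size {14}, are DGF of 28% and 15%, alpha 0.03 (taken as two-sided, as the Fig. 2 caption does for the subgroup level), 80% power and 20% nonevaluable.

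n = [z(0.985)·√(2·p̄·(1−p̄)) + z(0.80)·√(p1(1−p1) + p2(1−p2))]² / (p1−p2)², with p̄ = 0.215

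= [2.170·√0.33755 + 0.842·√0.3291]² / 0.13² ≈ 179.9, rounded up to 180 per group.

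180 / 0.80 = 225 pairs. Both stated figures reproduce. The allowance is 225 − 180 = 45 pairs. It covers pairs discordant for preservation method as well as nontransplanted grafts, and the discard share is not given.

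**2. Tracing a discarded kidney through the stated analyses.**

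| Analysis or data route | Compares discards by arm? | Why |
|---|---|---|
| Safety population with Safety analyses | No | Worded by subject; the test is on adverse events, which a kidney without a recipient cannot contribute |
| Incidents under Safety | No | Described for HEMO2life use only; discard not listed |
| Monitoring-board reports {21a} | No | Reported SAEs and AEs plus a summary of incidents during surgeries; timed by pairs that have reached one week after transplantation |
| Full Analysis Population {20a} | No | Complete, concordant pairs only |
| Extended Full Analysis Population {20a} | No | Takes all randomised grafts, but is an exploratory set, and DGF is undefined for a kidney never implanted |
| Missing data {20c} | No | Foresees a missing primary outcome only for deaths in the first week |

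The result does not depend on what a subject is. If the safety population is read as counting kidneys, the only test is still on adverse events, and pre-implantation incidents still have no stated control counterpart.

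**3. What a paired count could show.** The documents give no discard rate, so these splits are assumptions. They take the 260 donors expected under Recruitment {15} as 260 randomised pairs, with no pair losing both kidneys. Exact McNemar: p = 2·P(X ≤ smaller count), X ~ Binomial(total discards, 0.5). For 6 vs 0, p = 2·0.5⁶ = 0.031.

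| Discards, HEMO2life vs control | Exact McNemar p | Recipients left per arm |
|---|---|---|
| 5 vs 0 | 0.063 | 255 vs 260 |
| 6 vs 0 | 0.031 | 254 vs 260 |
| 8 vs 2 | 0.109 | 252 vs 258 |
| 10 vs 3 | 0.092 | 250 vs 257 |
| 13 vs 5 | 0.096 | 247 vs 255 |
| 26 vs 13 | 0.053 | 234 vs 247 |

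Under the stated safety set, read as recipients, each row would appear only as a difference in denominators. Most rows do not reach 0.05, so the counts and paired difference would tell the reader more than the p-value.

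**The case against.** The strongest reply has four parts.

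- **Subjects are not defined.** The sentence on preemptive grafts uses the graft as the unit, and it is the kidney that receives the treatment. This stands in part: recipients only is the natural reading, since subjects can drop out and a preemptive graft has a recipient, but it is not a stated definition. The conclusion survives either reading.
- **The nonevaluable rule is not a safety rule.** Recruitment {15} governs the count of pairs for the primary endpoint. This stands. That section shows that nontransplanted kidneys are expected. It does not remove them from safety reporting.
- **The signal has other routes.** Perfusion problems, contamination and abnormal appearance are on the incident list and need no recipient, and the monitoring board receives a summary of incidents during surgeries. This stands. A reader might infer that an excess of discards would go wholly unseen, or that a harmful product would necessarily be declared safe and effective; the documents do not support either. What is missing is the comparison with control kidneys.
- **Disposition by arm is routine.** The unseen analysis plan or a participant flow diagram may count discards. That is possible. But the protocol does fix a safety population and a safety test, and as fixed they leave out a graft-level outcome that falls within its own objective.

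**Conclusion.** The point holds in a limited form. The product is given to the kidney and safety is to be assessed "for the graft and the graft recipient", yet no safety analysis stated in the protocol compares kidneys not transplanted after randomisation between arms. HEMO2life incidents before a discard may still be described and reach the monitoring board.

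The size is unknown. No discard rate is given, and the splits shown above are assumptions. Nothing in the documents suggests that an excess of discards occurred or was expected. A reader might also want to count discards as DGF failures and restate the treatment effect; the protocol defines no such composite, and that would be an efficacy question rather than a measure of this gap.

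This is a worthwhile, low-cost improvement to the safety analysis. It rests on the wording of the Safety population and Safety analyses sections and on the HEMO2life-only incident collection.

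**What to change.** 1. In Safety population, state whether subjects means recipients. Keep the recipient set for adverse events, and add a graft-safety set of all randomised kidneys in both arms, transplanted or not.
2. In Safety analyses, add the outcome of not being transplanted after randomisation. Report it by arm, with the reason where available, and compare it within donor pairs by exact McNemar test, giving the counts and the paired difference.

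**Cost:** one extra table and a few lines of text. Arm and transplantation status must already be known in order to class a pair as nonevaluable. The real effort may lie in the reasons: incident collection is described only for HEMO2life, and Trial status puts the last inclusion in July 2022, so control-arm discard reasons may have to be retrieved afterwards. Where they cannot be, the count by arm is still worth reporting.

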### Trial design {8}

OxyOp2 is a prospective, multicenter, randomized, comparative, single-blinded, parallel-group, superiority study versus standard of care in renal transplantation. After the selection of a suitable donor according to the inclusion/exclusion criteria, both kidneys will be studied. Depending on the characteristics of the donor and following the French recommendations for organ preservation (Agence de la Biomédecine), both kidneys will be preserved either in cold storage or on machine perfusion (Fig. 1). Basically, grafts from standard donors are preserved in cold storage, whereas grafts from extended criteria donors are preserved on machine perfusion. Each kidney will be allocated to a patient following the French organ allocation rules independently of the protocol. In accordance with the rules for assigning kidney transplants in France, one kidney is allocated and transplanted locally (local kidney) in the transplant center where the kidney has been retrieved (local waiting list), whereas the contralateral kidney is allocated based on the national waiting list (national waiting list).

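### The first-step renal-function analysis assumes that dialysis is balanced between arms, which the trial's own hypothesis denies; at the early visits this pulls the eGFR comparison toward no effect

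*Protocol article*

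**What the plan says.** All references are to the Protocol article.

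- **Trial design {8}** describes a "single-blinded, parallel-group, superiority study versus standard of care in renal transplantation".
- **Outcomes {12}** makes the primary outcome the occurrence of "DGF, defined as the need for renal replacement therapy during the first week after transplantation". Renal function is a secondary outcome: creatinine and eGFR at Days 7, 14 and 30 and at months 3 and 12, with AUCs of both from D0 to D30. Another secondary outcome is the "time to reach a creatinine value of 250" µmol/l.
- **Sample size {14}** rests on "an expected DGF rate of 28% in the control arm" and "a 15% rate in the HEMO_2_life® arm".
- **Safety population** contains the rule on how these measures are handled: "only available data will be used in a first step that assumes that death and dialysis will be balanced in the two groups". The planned sensitivity analysis imputes instead, "using the last observation carried forward (LOCF) for deceased patients and a fixed value (eGFR = 5) for dialysis patients". No value is assigned for creatinine.
- **Secondary efficacy analyses** compares quantitative outcomes by the paired t test, or by the paired Wilcoxon test if normality fails. For time to 250 µmol/l it gives two ways of treating primary nonfunction and adds competing-risk models.
- **Plans for assessment and collection of outcomes {18a}** derives eGFR from creatinine by the MDRD formula and captures additional creatinine results in the first month.

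**The concern.** The first-step analysis needs dialysis to be equally frequent in both arms, while the primary hypothesis is that it is less frequent with HEMO2life. The early renal-function measurements cover or directly follow the week in which DGF is defined. If patients on dialysis are left out, the analysis conditions on a post-randomisation event that the product is meant to change. Control loses more of its worst grafts, and comparable grafts spared dialysis stay in the HEMO2life arm with low function.

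At stake is the reading of early eGFR. A product that works on DGF could appear to do little for early function, and the paired tests would discard many pairs. The article is not merely silent here: it states both the assumption and the order of the two analyses.

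**Working it through.** **1. Are 28% and 15% the plan's working rates?** Inputs from Sample size {14}: 28%, 15%, alpha 0.03 (taken as two-sided), power 80%. With pooled variance and no continuity correction:

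n = [2.170 × √(2 × 0.215 × 0.785) + 0.842 × √(0.28 × 0.72 + 0.15 × 0.85)]² / 0.13² = 180 per group.

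180 / 0.8 = 225 per group, or 450 in total. Both stated figures reproduce.

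**2. What do these rates imply for balance?** With 180 per arm, 0.28 × 180 = 50 control and 0.15 × 180 = 27 HEMO2life recipients are dialysed in week 1. Treating the arms as independent, the standard error of the difference is √(0.28 × 0.72/180 + 0.15 × 0.85/180) = 0.0428, so the expected gap is 0.13/0.0428 = 3.0 standard errors. The chance of an observed gap of 3 points or less is about 1%.

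**3. How many pairs are lost?** If every DGF patient lacks a usable value at the visit, the share of pairs losing at least one value is 1 − 0.72 × 0.85 = 39% with independent outcomes within pairs. It is 36% at a within-pair correlation of 0.2 and 34% at 0.3. These are upper bounds for loss through dialysis, because DGF means any dialysis in week 1, not dialysis at the visit.

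**4. How far is the eGFR difference attenuated?** Assumption: latent function is normal with a common SD, and patients still on dialysis are its lower tail. Let f be the share of DGF patients still on dialysis at the visit; the documents do not give it. The true shift in SD units is d = z(0.28f) − z(0.15f). The mean among those above the cut-off c = z(0.28f) is μ + φ(c − μ)/[1 − Φ(c − μ)], with μ = 0 for control and μ = d for HEMO2life.

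| f | on dialysis, control / HEMO2life | true shift (SD) | available-data difference (SD) | ratio |
|---|---|---|---|---|
| 1 | 28% / 15% | 0.454 | 0.260 | 57% |
| 0.5 | 14% / 7.5% | 0.359 | 0.253 | 71% |
| 0.1 | 2.8% / 1.5% | 0.259 | 0.231 | 89% |

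For f = 1, restricting a simulation to complete pairs gave 0.259 SD with independent kidneys (57%) and 0.312 SD at a latent within-pair correlation of 0.3 (0.312/0.454 = 69%).

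On an illustrative scale (SD 18, control mean 30, both assumed; f = 1), the true shift is 8.2 ml/min. The available-data difference is 43.1 − 38.4 = 4.7, and the eGFR = 5 rule gives 8.3.

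**5. Can the sign reverse?** Assumption: the product helps only the 13% spared dialysis, who have eGFR 15, and all other undialysed patients have 40. Available data give (0.72 × 40 + 0.13 × 15)/0.85 − 40 = −3.8. The eGFR = 5 rule gives 0.13 × (15 − 5) = +1.3. With eGFR 10 to 20 in the spared and 35 in the others, the two results are −3.8 to −2.3 and +0.7 to +2.0. If the other 72% of HEMO2life kidneys also gain 4.5 ml/min, the reversal disappears: (0.72 × 44.5 + 0.13 × 15)/0.85 − 40 ≈ 0.

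**The case against.** The strongest reply is that the plan states its assumption openly and prespecifies the eGFR = 5 analysis in the next sentence, so both results will be available. Renal function is one of several unranked secondary outcomes. The confirmatory strategy concerns DGF alone, and its McNemar test is untouched. All of this stands and limits the severity. It does not explain why the analysis whose assumption the design contradicts should come first.

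It is also true that leaving out dialysis patients is inferred from the words on available data. It is the natural reading, because the balance assumption is needed only if those patients are absent and they receive a value only in the sensitivity analysis. Since eGFR is calculated from creatinine, values taken on dialysis must be either in or out for both measures. If out, steps 3 to 5 apply. If in, no pairs are lost, but values lowered by dialysis enter, more often in control, and do not measure graft function. Both readings work against the product.

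A reader might infer four stronger points that the documents do not support:

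- **The early results will reverse.** This needs benefit confined, or nearly so, to the rescued kidneys, with eGFR levels that the article does not give.
- **The product could gain a false benefit.** With no effect on DGF, no imbalance is expected.
- **Creatinine has no rule at all.** Secondary efficacy analyses covers primary nonfunction and competing risks for time to 250 µmol/l. The gap is narrower: values taken during temporary dialysis.
- **LOCF for deaths is a comparable defect.** The article gives no expected difference in deaths, and deaths are analysed separately as patient survival and as graft failure.

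**Conclusion.** The point holds for early renal function: Day 7, Day 14, possibly Day 30, and the D0-D30 AUC. There the first-step assumption contradicts the hypothesis and the rates on which the trial is sized. If the product works, the expected consequence is attenuation of the eGFR difference, to between 57% and 89% of its true size as f runs from 1 to 0.1, with up to 39% of pairs lost to the paired test. The direction follows from the plan's own 28% and 15% when dialysis marks the poorest grafts. The size rests on the assumed normal model and on the unknown share still on dialysis at each visit.

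The problem shrinks by months 3 and 12 as patients leave dialysis. Severity is moderate, because only secondary outcomes are touched and the better eGFR analysis is already planned.

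**What to change.** - For early eGFR and its D0-D30 AUC, make the planned analysis with eGFR = 5 for patients on dialysis the lead analysis. Compare arms with the paired Wilcoxon test, which the plan already allows, because the fixed value creates a spike. Keep the available-data analysis as sensitivity.
- Withdraw the statement that dialysis is assumed balanced.
- State whether values taken on dialysis count as available, with one answer for creatinine and eGFR.
- For creatinine, do not count values taken on dialysis as recovered function in the D0-D30 AUC or in time to 250 µmol/l. This adds to the primary nonfunction rules and does not replace them.

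The cost is wording, settled before renal function is compared by arm; no new analysis of eGFR is needed. Applying the creatinine rule requires knowing which values were taken on dialysis. The downside is that a mean eGFR difference depends on the chosen value of 5, so the rank-based result, which is less sensitive to it, should be given.
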